## Analysis of outcomes

Repeated-measures analysis of variance (ANOVA) with drug (MDMA and duloxetine) as within-subject factors followed by Tukey’s post-hoc tests will be use to analyze differences between the different treatment conditions. Transformations will be performed before analysis, if response variables are nonnormally distributed. Pharmacokinetic parameters (Cmax, tmax, AUC from 0 to 6 h) will be obtained using *PK Functions for Excel*®. AUC values will be calculated by the trapezoidal rule. Additional PK analyses may be performed using *WinNonLin®* and *GraphPad®.* Statistical analyses will be performed using *Statistica*® *(StatSoft).*

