# STUDY DESIGN AND METHODS

## Study design

We will use a double-blind cross-over design with four treatment conditions. Treatment conditions are placebo-placebo, duloxetine-placebo, placebo-MDMA, and duloxetine-MDMA. Order will be balanced and pseudo-random. Each subject will participate in four 1-day study sessions with a washout period of two weeks (>10 days) between sessions. We previously used similar designs [18].

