## Study population

### Recruitment

Subjects will be recruited by word of mouth and by advertisements placed on advertising boards of university institutes of the University of Basel and on the homepage of the University. Similar to previous studies [18], we intend to include mainly healthy University students. Six-teen male or female subjects will be enrolled. Drop-outs will be replaced.

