### Randomization and Blinding

Each subject will receive all treatments. Subjects and study personnel will be blinded to treatment order. Order is balanced and pseudo-random. A study subject number will be assigned to each subject. A treatment order is assigned to each subject number (code). Treatments are prepared and labeled according to the code by a pharmacist not involved in the study. The PI will also receive the code enclosed in an envelope. In case of a medical emergency the code can be accessed.

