# Data analysis

## Sample size estimation

Power analysis was performed with PASS®, Hintze J. Kaysville, Utah, US. We consider a relative reduction of 20% (MDMA vs. duloxetine+MDMA) in “good drug effects” to be clinically meaningful [13, 16, 17, 68]. A sample size of 13 achieves 82% power to detect a difference of 20 between the null hypothesis mean of 100 and the alternative hypothesis mean of 80 with a known standard deviation of 25 [13, 68] and with a significance level (alpha) of 0.05 using a two-sided one-sample t-test. For the most relevant secondary outcome, which is Psys, we expect that duloxetine will decrease the MDMA-induced increase in Psys by 10 mmHg from +30 mmHg (MDMA vs. placebo) to +20 mmHg MDMA+duloxetine vs. duloxetine). This effect of duloxetine would be relevant and similar to the one of citalopram on MDMA-induced increases in Psys [15]. A sample size of 8 achieves 81% power to detect a difference of 10 between the null hypothesis mean of +30 and the alternative hypothesis mean of +20 with a known standard deviation of the difference of 10 [15] and with a significance level (alpha) of 0.05 using a two-sided one-sample t-test. Assuming a drop-out rate before inclusion of 50% we will have to screen 32 subjects to include 16 in the study. Lower (8-12) [16, 17] or similar sample sizes [13, 47, 68, 82] were used in previous comparable studies. Subjects who prematurely discontinued the study for any reason will be replaced if the number of discontinued subjects exceeds three. A samples size of 8 or less is commonly used in PK studies. A larger sample is used here to produce meaningful results for the pharmacodynamic parameters.

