### Replacement policy

Subjects who withdraw from the study will be replaced if the number exceeds three subjects, to maintain at least 13 subjects. Replacement subject will follow the same treatment sequence as the withdrawn subject.

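### The four-session crossover is analysed with only the two drugs as named factors, so any period effect inflates the error, unreplaced withdrawals can unbalance the orders, and incomplete subjects would normally be dropped

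*Protocol*

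**What the plan says.** Section 10.1 sets the design: "We will use a double-blind cross-over design with four treatment conditions". It continues: "Each subject will participate in four 1-day study sessions with a washout period of two weeks (>10 days) between sessions". On order it says "Order will be balanced and pseudo-random", and section 11.5.5 repeats this. The sequences themselves are not listed.

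Section 13.2 gives the analysis: "Repeated-measures analysis of variance (ANOVA) with drug (MDMA and duloxetine) as within-subject factors followed by" Tukey's tests between conditions. It names no period, session or sequence term, and no rule for a subject with a missing session.

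On numbers, section 10.4.1 says "Six-teen male or female subjects will be enrolled", and section 13.1 says "A sample size of 13 achieves 82% power to detect a difference of 20". Under section 14.4.7, "Subjects who withdraw from the study will be replaced if the number exceeds three subjects", so that at least 13 remain; a replacement takes over the withdrawn subject's sequence. Section 13.1 has the same threshold of three. Section 10.4.1 instead says, without any threshold, that drop-outs are replaced.

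**The concern.** The design controls for session order by balancing it, but the stated model does not then remove it. The washout deals with carry-over, not with a general change from the first to the fourth session. The primary outcome is a subjective rating of good drug effect, in volunteers with little experience of illicit drugs other than cannabis (section 10.4.3 limits prior use to five times but exempts THC products). Novelty at the first session or later habituation is therefore credible.

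Three things are at stake:
- **Precision.** With balanced orders, a period effect that is not modelled sits in the error term.
- **Balance.** Taking over the withdrawn subject's sequence protects balance only from the fourth withdrawal on. Three losses without replacement can leave the two MDMA conditions unevenly spread over sessions.
- **Incomplete subjects.** A classical repeated-measures ANOVA needs all four sessions. A subject with both MDMA sessions but one missed placebo session would normally be lost to the primary comparison. The protocol foresees ways for this to happen: a positive drug screen (section 11.2.4) and withdrawal for adverse events or other reasons (section 14.4.6).

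**Working it through.** **Inputs.** Section 13.1 gives a difference of 20 (100 against 80), SD 25, two-sided alpha 0.05 and n = 13. Section 10.4.1 gives 16 enrolled. The 100 and 80 express a relative reduction, so all points below are on that scale. Assumed here: a linear drift of 0, 5 or 10 points per session, and SD 25 as the period-free SD of the paired difference (duloxetine-MDMA minus placebo-MDMA).

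**1. The plan's own figure.** With a known SD, power = Φ(20·√13/25 − 1.96) = Φ(2.884 − 1.96) = 82.2%, which reproduces the stated 82%. With an estimated SD (noncentral t), n = 13 gives 75.4% and n = 16 gives 84.8%. The t figures are used from here on.

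**2. Error inflation with balanced orders.** A subject whose two MDMA sessions lie g periods apart has a contrast shifted by ±g × drift. These shifts cancel in the mean but add variance: SD = √(625 + drift² × mean g²).

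Over all 24 orders, mean g² = (3·1 + 2·4 + 1·9)/6 = 3.33. Williams squares, one common way to balance four conditions, give 2.5 (gaps 1, 1, 2, 2) or 5.0 (gaps 1, 1, 3, 3), depending on how the conditions are labelled.

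| Orders | SD, drift 5 | SD, drift 10 | Power n = 16, drift 5 | Power n = 16, drift 10 |
|---|---|---|---|---|
| All 24 | 26.6 | 31.0 | 80% | 68% |
| Williams, gaps 1 and 2 | 26.2 | 29.6 | 81% | 72% |
| Williams, gaps 1 and 3 | 27.4 | 33.5 | 78% | 61% |

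With no drift, power is 85% in every row. Under balance, the true sampling spread of the contrast does not grow; its standard error is overstated. A simulation of the gaps 1 and 2 case with drift 10 and no treatment effect gave a type I error of 2.3% against the nominal 5%, so the test is conservative. The same case with the full effect gave simulated power of 75%, slightly above the formula's 72%.

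**3. Bias after three losses.** The shifts sum to zero over 16 balanced subjects. Removing three subjects with the same signed gap g leaves a mean shift of 3g/13 × drift in absolute size:
- g = 2: 6/13 = 0.46 periods, or 2.3 points (drift 5) and 4.6 points (drift 10).
- g = 3: 9/13 = 0.69 periods, or 3.5 and 6.9 points.

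If the three losses are random across orders (gaps 1 and 2 case), the bias averages zero, with SD about 1 point (drift 5) or 2 points (drift 10). A gap of three does not occur in two of the three Williams labellings. In the third, the chance that three random losses all come from one gap-three sequence is 2·C(4,3)/C(16,3) = 8/560 = 1.4%.

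**4. Dropping incomplete subjects.** With no drift, going from 16 to 13 takes power from 85% to 75%. In simulation (gaps 1 and 2), three subjects missed their last session at random, with drift 0, 5 or 10. Complete subjects without period gave 76%, 71% and 60%. All available sessions with subject, period and treatment in the model gave 86%, 85% and 84%. Part of that gain is not due to period: with all 16 complete and no drift, the second model has about 88% against 85%, because it pools the error over more degrees of freedom.

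**5. What a period term does not remove.** Suppose drift of 10 occurs only in MDMA sessions and three subjects are lost from one sequence. An additive period term then leaves 3.0 of 4.6 points (gap 2) or 4.5 of 6.9 (gap 3), about 65% of the bias. If the drift is common to all sessions, the remaining bias is zero.

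**The case against.** The strongest reply is that section 13.2 is a short summary. It never says that the drugs are the sole factors, and nuisance terms and missing-session rules often stand in a statistical analysis plan, which is not at hand. Part of this stands: casewise deletion is inferred from the named method. But the section does name a model and its factors, and that model does not match the design.

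Second, the planned analysis is valid while orders are balanced: unbiased and, if anything, conservative. This stands. A reader might infer that the planned analysis gives a biased duloxetine effect, or that a subject with a missed session is certain to be lost. The documents support neither. Bias needs both a period effect and unbalanced losses, and no deletion rule is written.

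Third, the drift is assumed. The SD of 25 comes from earlier studies; if those were crossovers analysed without period, it may already contain period variance, and step 2 would overstate the loss. This stands as a limit on size. The loss in step 4 does not depend on drift.

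Fourth, attrition is provided for: 16 are enrolled to keep 13, and if section 10.4.1 governs, every drop-out is replaced and the three-loss scenario falls away. But sections 13.1 and 14.4.7 say otherwise, and 13 subjects give 75% power once the SD has to be estimated.

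**Conclusion.** The point holds as a recommended improvement to a stated method; it does not show the planned analysis to be invalid. With balanced orders the cost is precision only: power with 16 subjects falls from 85% to about 80% to 68% for an assumed drift of 5 to 10 points per session, and not at all without drift. With three unreplaced withdrawals, the bias averages zero if losses are random across orders. It reaches about 2 to 5 points of the 20 sought in an unfavourable case, and 7 only in a rare worst case. If incomplete subjects are dropped, as the named method would normally require, going from 16 to 13 cuts power from 85% to 75% whatever the period effect. The sizes rest on the assumed linear drift, on SD 25 being free of period variance, and on sequences that the protocol does not give.

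**What to change.** In section 13.2, replace the repeated-measures ANOVA with a linear mixed model: MDMA, duloxetine, their interaction and period as fixed effects, and subject as a random effect. Allow different variances in MDMA and non-MDMA sessions, since ratings of good effect on placebo are plausibly near the floor and a common error could misstate that of the MDMA contrast. Use all completed sessions, and take the primary contrast (duloxetine-MDMA against placebo-MDMA) from this model.

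As a sensitivity analysis, let the period effect differ between MDMA and non-MDMA sessions, because an additive term only partly removes drift confined to MDMA sessions. Reconcile section 10.4.1 with sections 13.1 and 14.4.7 on replacement of drop-outs.

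The cost is analysis wording and 3 degrees of freedom for period. In a least-squares count with 16 complete subjects, error degrees of freedom go from 64 − 16 − 3 = 45 to 42. The model does not rescue a subject who missed one of the two MDMA sessions: that subject still gives no direct within-subject primary contrast, so selection by tolerability is only partly relieved.

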### Physiological assessments

#### Vital signs

Blood pressure, heart rate, body temperature, and pupil diameter will be recorded at -4 h, 0, 20, 40, 60, 90, 120, 150, 180 min, and 4, 5, and 6 h after MDMA/placebo administration. Blood pressure (systolic and diastolic) and heart rate will be measured on the leading arm using an automatic oscillometric device. Heart rate will also be measured continuously with a RS 800 Polar device (Polar Electro Oy, Kempele, FIN), set to sample the average heart rate every 5 s, and analyzed using Polar Precision Performance software. Body temperature will be measured using an ear thermometer. Ambient temperature is also recorded trice on the experimental day. Pupil diameter and the reaction to a light stimulus will be recorded using a handheld dynamic pupillometer (PRL-200, Neuroptics, Irvine, CA, USA).

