### Neuroendocrine function

MDMA increases cortisol, prolactin, catecholamine, and 5-HT concentrations in plasma in humans [43, 57-59]. MDMA also increases vasopressin (AVP) potentially leading to hyponatriemia [59, 60]. We will test the effect of duloxetine on MDMA-induced increases in plasma cortisol, prolactin, catecholamines, serotonin, and metanephrines (norepinephrine and epniephrine metabolites). Plasma cortisol and prolactin samples will be collected at 0 min and at 120 min (tmax) after MDMA/placebo administration (2x7.5 ml blood). Copeptin is the C-terminal part of provasopressin. Copeptin is released stoichiometrically together with AVP and is easier to measure than AVP. Copeptin samples will be collected at 0 min and 120 min after MDMA/placebo administration when peak AVP values are expected [59] (2x7.5 ml blood). Plasma and urine sodium, urea, and osmolality are simultaneously assessed (2x7.5 ml blood, 2x10 ml urine). Catecholamine and metanephrine samples will be collected at 0, 60, and 120 min after MDMA/placebo administration (3x7.5 ml blood).

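### The 0 min pre-MDMA reading taken in every session has no role in the stated ANOVA; using it as a covariate for the MDMA-by-duloxetine interaction is an optional, low-cost gain in precision

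*Protocol*

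**What the plan says.** Protocol section 13.2 (Analysis of outcomes) gives one model for all outcomes: "Repeated-measures analysis of variance (ANOVA) with drug (MDMA and duloxetine) as within-subject factors", with Tukey tests afterwards. It names no covariate and does not define the response variable.

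Each session has a reading at the time of MDMA or placebo:

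- Section 11.4.2.1 (Vital signs): measures "will be recorded at -4 h, 0, 20, 40, 60, 90, 120, 150, 180 min, and 4, 5, and 6 h after MDMA/placebo administration".
- Section 11.4.4 (Neuroendocrine function): "Plasma cortisol and prolactin samples will be collected at 0 min and at 120 min (tmax) after MDMA/placebo administration"; "Copeptin samples will be collected at 0 min and 120 min after MDMA/placebo administration"; "Catecholamine and metanephrine samples will be collected at 0, 60, and 120 min after MDMA/placebo administration".

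Section 13.1 (Sample size estimation) names systolic pressure (Psys) as the most relevant secondary outcome. It expects that "duloxetine will decrease the MDMA-induced increase in Psys by 10 mmHg from +30 mmHg (MDMA vs. placebo") to +20 mmHg for MDMA plus duloxetine against duloxetine alone. The target is therefore a difference of two differences, which is the MDMA-by-duloxetine interaction.

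**The concern.** A crossover removes stable differences between subjects. It does not remove variation between one subject's four sessions, which are about two weeks apart. The 0 min value measures part of that variation, and a model with only the two drug factors leaves it in the error.

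For the interaction, 0 min is a proper baseline. Each of the two differences compares sessions with the same pretreatment, so any effect of duloxetine itself on the 0 min value cancels. What is at stake is precision for Psys and the neuroendocrine endpoints in a trial of 16 subjects that may finish with 13 (section 14.4.7). Validity is not at stake.

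**Working it through.** **Inputs from the protocol.** Psys effect 10 mmHg; SD of the difference 10, treated as known; two-sided alpha 0.05; n = 8 for the stated 81% power (13.1); 16 planned (13.1); at least 13 completers (14.4.7).

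**Assumed input.** r, the within-subject, session-level correlation of the 0 min and post-dose values. The protocol gives none; the range used is 0 to 0.7.

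**Stated figure.** With known SD, power = Φ(10 × √8 / 10 − 1.960) = Φ(0.868) = 0.807, which reproduces the 81%. All power figures below use the noncentral t, with the SD estimated.

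**Effect of the covariate.** The contrast SD is multiplied by √(1 − r²) and one degree of freedom is lost. Variance falls by r²: 0.3² = 9%, 0.5² = 25%, 0.7² = 49%. A change from 0 min multiplies the SD by √(2(1 − r)), which is below 1 only when r exceeds 0.5.

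**Which SD?** Section 13.1 can be read in two ways. If 10 is the SD of the tested contrast, it is used directly. If 10 is the SD of one paired difference, the contrast of two such differences has SD 10 × √2 = 14.1.

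Power for 10 mmHg, with n − 1 df unadjusted and n − 2 df with the covariate:

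| Contrast SD | n | Unadjusted | Covariate, r = 0.3 / 0.5 / 0.7 | Change score, r = 0.3 / 0.5 / 0.7 |
|---|---|---|---|---|
| 10 | 13 | 91.1% | 93.0 / 96.6 / 99.6% | 79.9 / 91.1 / 98.9% |
| 10 | 16 | 96.2% | 97.3 / 99.0 / 99.9% | 88.4 / 96.2 / 99.8% |
| 14.1 | 13 | 64.9% | 68.3 / 76.4 / 90.1% | 50.9 / 64.9 / 85.5% |
| 14.1 | 16 | 75.3% | 78.7 / 85.9 / 95.7% | 60.9 / 75.3 / 92.6% |

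At SD 10 the covariate adds 1.9 / 5.5 / 8.5 points at n = 13 and 1.1 / 2.8 / 3.7 at n = 16. At SD 14.1 and r = 0.5 it adds 11.5 and 10.6 points. At r = 0 and SD 10 it costs about half a point at n = 13 (91.1% to 90.6%) and 0.2 at n = 16 (96.2% to 96.0%).

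A model with subject and condition effects that pools its error over 3(n − 1) df starts higher at SD 14.1: about 70% at n = 13 and 79% at n = 16 in simulation, rising to about 80% and 88% at r = 0.5. The higher start comes from pooling and is not a benefit of the covariate.

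**Bias check.** Assume duloxetine alone raises pressure by 5 mmHg at 0 min and later, MDMA adds 30 and the interaction is −10.

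- Interaction: about −10 in simulation, raw or adjusted. Type I error in null runs was 4.7% to 5.3%.
- Direct comparison of duloxetine-MDMA with placebo-MDMA: the true value is 5 − 10 = −5. Adjustment subtracts r × 5, giving −6.5 / −7.5 / −8.5 at r = 0.3 / 0.5 / 0.7. A change score gives −10.

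Adjustment leaves the interaction intact but exaggerates the direct effect of duloxetine in this setting.

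**The case against.** Section 13.2 is brief and does not say whether the response is a raw value, a peak, a change from 0 min or an area. A statistical analysis plan, which is not shown, could settle that. The 2×2 repeated-measures ANOVA is a valid test of the interaction, so preferring a covariate is a choice about efficiency. On the literal reading of the SD, Psys power is already above 90%. The correlation is an assumption, and the change divides a single ANOVA-plus-Tukey scheme into adjusted and unadjusted parts.

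Most of this stands, and it sets the weight of the point. A reader might infer that the plan has decided to discard baseline. The text does not support that, because a baseline-corrected response is not excluded. What remains is that 13.2 commits to a specific model in which the 0 min reading has no place, although the data will exist. The open response variable also leaves room for a change score, which does worse than no adjustment when r is below 0.5.

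**Conclusion.** The point holds as an optional, low-cost improvement. For vital signs and neuroendocrine measures, the stated model leaves session-to-session variation in the error that the 0 min value could partly remove. The reduction in error variance is r², and r is unknown.

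A reader might infer that the trial gives away substantial power on Psys. The documents do not support this. With 10 mmHg as the contrast SD, the gain is 2 to 9 points from about 91% (n = 13) and 1 to 4 points from about 96% (n = 16) for r from 0.3 to 0.7. It is larger, about 11 points at r = 0.5, only if 10 mmHg is the SD of one paired difference. Near r = 0 there is no gain and a very small loss. If the SD of 10 already comes from baseline-corrected data, which the protocol does not say, there may be no further gain. For the hormones the protocol states neither an SD nor power, so no loss can be quantified.

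A reader might also infer that every comparison should be adjusted. It should not: 0 min follows both duloxetine doses, so adjustment distorts comparisons across pretreatments.

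**What to change.** In section 13.2, for vital signs and neuroendocrine measures:

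- Estimate the MDMA-by-duloxetine interaction from a within-subject linear model with subject and condition, and the same session's 0 min value as covariate, for whichever post-dose response is chosen.
- Keep the direct comparison of duloxetine-MDMA with placebo-MDMA, and all other comparisons between sessions with different pretreatment, unadjusted. Say that the Tukey tests across pretreatments are of this kind.
- Leave the primary VAS analysis unchanged; 0 min scores are expected to lie near zero and would add little.
- Do not use a raw change score in place of the covariate.

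The cost is a short addition to 13.2, one degree of freedom, the assumption of a common slope on the 0 min value across conditions, and separate reporting of adjusted and unadjusted contrasts. No new data are needed.

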# HYPOTHESES

## Primary Hypotheses

1. Duloxetine will attenuate positive mood effects of MDMA. Specifically, co-administration of duloxetine with MDMA will result in a relative decrease in “good drug effects” VAS scores by 20% compared to the MDMA alone condition.

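### The primary comparison is sized as a single paired t-test at 0.05, but the only between-condition test the protocol states is Tukey's over four conditions

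*Protocol*

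**What the plan says.** - **Primary hypothesis (Protocol 9.1).** Duloxetine given with MDMA lowers the good-drug-effects VAS by 20% "compared to the MDMA alone condition". This is one contrast between two of the four conditions.
- **Conditions (Protocol 10.1).** "Treatment conditions are placebo-placebo, duloxetine-placebo, placebo-MDMA, and duloxetine-MDMA". Each subject receives all four.
- **Sizing (Protocol 13.1).** "A sample size of 13 achieves 82% power to detect a difference of 20" between means of 100 and 80, "with a known standard deviation of 25" and "with a significance level (alpha) of 0.05 using a two-sided one-sample t-test". For systolic blood pressure: "A sample size of 8 achieves 81% power to detect a difference of 10", with an SD of the difference of 10.
- **Analysis (Protocol 13.2).** A repeated-measures ANOVA with MDMA and duloxetine as within-subject factors, after which Tukey's "post-hoc tests will be use to analyze differences between the different treatment conditions". No contrast is singled out as primary and no error term is named. The section adds: "Transformations will be performed before analysis, if response variables are nonnormally distributed".
- **Numbers (Protocol 10.4.1 and 14.4.7).** Sixteen subjects are enrolled. Up to three withdrawals may go unreplaced, so that at least 13 remain.

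**The concern.** Sections 9.1 and 13.1 agree with each other: one question, one paired comparison, tested at 0.05. Section 13.2 describes a different procedure. Tukey's test protects the error rate over every pair of conditions. With four conditions there are 4 × 3 / 2 = 6 pairs, and five of them are not the primary question. Nothing in 13.2 exempts the primary pair.

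This is a conflict between two statements in the protocol, not a detail left for later. An analysis plan that followed 13.2 faithfully would carry it forward. At stake is whether the trial has the power it claims for its one primary question. The level and power of that test may also come to depend on how scores vary in two conditions that the hypothesis does not concern.

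**Working it through.** **Inputs.** From 13.1: difference d = 20, SD s = 25, two-sided alpha 0.05, n = 13. From 10.4.1: n = 16 enrolled. Section 13.1 does not label the 25 as the SD of the difference (it does label the blood-pressure SD so). It is read that way here because a one-sample test implies it.

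**Step 1: the protocol's own figure.** With λ = d / (s/√n):
- n = 13: λ = 20 / (25/√13) = 2.884. With known SD, power = Φ(2.884 − 1.960) = 82.2%, which reproduces the stated 82%.
- The named t-test at n = 13 (12 df, critical value 2.179, noncentral t) gives 75.4%.
- n = 16: λ = 20 / (25/4) = 3.2. The t-test (critical value 2.131) gives 84.8%.
- Blood pressure at n = 8: known SD 80.7% (stated 81%), t-test 68.1%.

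Both stated powers are therefore known-SD figures, although the text names a t-test.

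**Step 2: Tukey over four conditions, equal variances.** The critical |t| is q(0.95; 4, df)/√2, and power comes from the noncentral t with the same λ. Two error df are shown because the protocol names no error term.

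| n | error df | q | critical \|t\| | level for the pair | power | paired t-test power |
|---|---|---|---|---|---|---|
| 13 | 36 = 3(n−1) | 3.81 | 2.69 | 0.011 | 57.9% | 75.4% |
| 13 | 12 = n−1 | 4.20 | 2.97 | 0.012 | 49.4% | 75.4% |
| 16 | 45 = 3(n−1) | 3.77 | 2.67 | 0.011 | 70.1% | 84.8% |
| 16 | 15 = n−1 | 4.08 | 2.88 | 0.011 | 62.8% | 84.8% |

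For 80% power the paired t-test needs n = 15. Tukey needs 20 with 3(n−1) error df, or 22 with n−1.

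Of the fall from 82.2% to 57.9% at n = 13, 82.2 − 75.4 = 6.8 points come from the known-SD sizing and 75.4 − 57.9 = 17.5 points from Tukey.

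**Step 3: unequal variances.** Scores without MDMA may sit near the floor of the VAS with little spread. The protocol gives no SD for those conditions, so this step rests on assumptions: SD of the MDMA-cell difference held at 25, non-MDMA SD from 0 to 18, correlation ρ between the two MDMA cells from 0 to 0.7, and non-MDMA scores independent of the rest. Simulated results at n = 13 (20,000 runs per setting) are shown as false-positive rate / power for the primary pair:

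| non-MDMA SD | Tukey, pooled error, ρ = 0 | Tukey, pooled error, ρ = 0.7 | Tukey, interaction error |
|---|---|---|---|
| 0 | 7.1% / 83.3% | 0.6% / 46.4% | 5.5-6.0% / 78% |
| 5 | 5.9% / 81.5% | 0.5% / 43.9% | about 5% / 75-76% |
| 10 | 3.6% / 75.3% | 0.4% / 38.7% | 3.1-3.5% / about 68% |
| 18 | 1.0% / 57.5% | 0.1% / 26.9% | about 1.1% / 49% |

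The paired t-test stays at about 5% and 75-76% throughout. With a non-MDMA SD of 3, pooled-error power at n = 13 is 83%, 75%, 65% and 46% for ρ = 0, 0.3, 0.5 and 0.7, with a false-positive rate from 0.7% to 7%. The interaction error gives about 77% power and a rate of about 5.5%.

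The direction can be checked by hand for a non-MDMA SD of 0. The contrast's own error variance is 25²/2 = 312.5.
- ρ = 0: the MDMA-cell variance is 312.5. Pooling over four cells gives 312.5/2 = 156.25, half the right value, so the test is too liberal.
- ρ = 0.7: the MDMA-cell variance is 312.5/0.3 = 1041.7. Pooling gives 1041.7/2 − 0.7 × 1041.7/6 = 399.3, above 312.5, so the test is too strict.

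**The case against.** The strongest reply is that the equal-variance figures may not describe this trial. If scores without MDMA are nearly constant, variances are not equal. Section 13.2 specifies two within-subject factors, which makes a separate interaction error term a natural reading. With that term and a non-MDMA SD of 0 to 5, Tukey's test has 75-78% power at n = 13 and a level of 5-6%, so nothing is lost against the paired t-test. An analysis plan that is not shown could also name the error term. All of this stands, and it rules out several stronger readings that a reader might infer:

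- **That the protocol uses a pooled error.** It names no error term. Pooling is a common form of Tukey's test after ANOVA, but here it would be an inference.
- **That power is necessarily cut.** This holds under equal variances. With nearly constant non-MDMA scores the result runs from a slight gain to a large loss.
- **That the false-positive rate is inflated.** Over most of the range examined the test is conservative. It exceeds 5% only when non-MDMA spread is small, and with pooled error only when the MDMA cells are also weakly correlated.
- **That the primary VAS will be transformed away from the 20% reduction.** The transformation sentence is a general rule for all outcomes. The protocol does not say that it will be triggered here or on which quantity normality is judged.
- **That the whole gap from 82% is due to Tukey.** Part of it is the known-SD sizing, and a paired t-test at n = 13 would not restore 82%.

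The reply does not remove the mismatch. Sections 13.1 and 13.2 still name different tests for the same question.

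**Conclusion.** The point holds as an inconsistency that should be fixed: the primary comparison was sized with one test and is to be analysed with another. Under equal variances, with 25 as the SD of the difference, the primary pair is tested at about 0.011. Power is then 15 to 22 points lower than the paired t-test at n = 16 and 17 to 26 points lower at n = 13, the floor allowed by the replacement policy.

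If non-MDMA scores are nearly constant (assumed SD 3), power at n = 13 can lie anywhere from about 46% to 83% and the level from under 1% to about 7%, depending on the error term and the correlation between the MDMA cells. There is no loss under the interaction error term. The protocol does not fix which case applies, so neither a certain loss of power nor an inflated false-positive rate is supported. What is supported is that the primary test's properties should not rest on these unknowns when a paired contrast avoids them.

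**What to change.** 1. In 13.2, name one primary test: a two-sided 0.05 paired contrast of duloxetine-MDMA against placebo-MDMA on the good-drug-effects VAS, using the within-subject difference for its error, without Tukey adjustment, and reported with a 95% confidence interval.
2. Keep the repeated-measures ANOVA and Tukey tests as secondary analyses of the remaining comparisons.
3. In 13.1, restate the primary power for the t-test it names: 75% at n = 13 and 85% at n = 16. State that the SD of 25 is that of the within-subject difference, if it is.
4. If Tukey is to remain the primary procedure, justify the sample size for it instead. Under equal variances, 80% power needs 20 subjects, or 22 with n−1 error df.

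Items 1 to 3 cost a paragraph in 13.2 and a sentence or two in 13.1. They need no new data or subjects, and should be settled before unblinding.
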